### Inclusion and exclusion criteria

Patients may be included if they are more than 65 years old and have MM. We will use a previously proposed definition of MM as the presence of two or more of the following chronic conditions: hypertension, depression or anxiety, chronic musculoskeletal conditions causing pain or limitation, arthritis and/or rheumatoid arthritis, osteoporosis, asthma, chronic obstructive pulmonary disease (COPD), ischemic heart disease, peripheral artery disease, heart failure, cerebrovascular diseases, chronic stomach or colon conditions, chronic hepatitis, diabetes mellitus, thyroid disorders, any active cancer in the previous five years, chronic kidney disease, chronic urinary conditions, hyperlipidemia, and obesity [22]. In addition, participants must have access to their smartphones. Exclusion criteria will include: patients who are sufficiently physically active, defined with International Physical Activity Questionnaire - Short Form (IPAQ-SF) > 150 min aerobic physical activity per week, an existing absolute contraindication for PA according to the American College of Sports Medicine (acute myocardial infarction within two days, ongoing unstable angina, uncontrolled cardiac arrhythmia with hemodynamic compromise, active endocarditis, symptomatic severe aortic stenosis, decompensated heart failure, acute pulmonary embolism, pulmonary infarction, deep venous thrombosis, acute myocarditis or pericarditis, acute aortic dissection, physical disability that precludes safe and adequate testing), poor comprehension of Portuguese language, disabling neurological disorder (defined as mRankin score $$\ge$$ 4), severe psychiatric illness, learning disability, dementia and cognitive impairment, registered blind, housebound or resident in a nursing home, non-ambulant, advanced cancer, and scheduled for surgery within five months after the first consultation. Orthopedic or rheumatologic diseases with severe impairment and chronic pain syndromes with inherently reduced mobility will also not be included.

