### Study intervention

All Participants who are eligible and consented to participate in the study shall receive PA promotion content in accordance to the Swedish model [23]. This method consists of five core components: (1) person-centered health promotion consultation; (2) a written prescription of physical activity; (3) a prescription guided by evidence-based knowledge on physical activity in the prevention and treatment of health conditions; (4) a follow-up of the written prescription; and (5) collaboration between the healthcare service and physical activity organizers outside healthcare. It is also emphasized that the method should be tailored to the local conditions in healthcare organizations. More specifically, we will recommend PA and provide informative flyers according to the Portuguese National Healthcare Authority and the World Health Organization recommendations for older age people. In addition to PA promotion counseling, all patients will be randomly allocated to either the intervention or the control groups using block randomization generated by a computer-generated random number sequence^1^. The allocation sequence will be generated by a research assistant who will not be involved in the data collection process. Eligible participants will be randomly assigned in a 1:1 ratio to one of the following intervention arms: Arm A (experimental arm), use of the device activity watch (Fitbit Sense), and a sleep monitoring mattress (Withings SA, France - Sleep Analyzer); Arm B (control): non-use of the devices. Participants randomized to wearable device BCT (Arm A) will be provided goal setting, self-monitoring and feedback. On the first visit they will undergo a brief training session where they’ll learn how to effectively use both devices, sync their data, and interpret the feedback they receive. Arm A participants will receive weekly feedback based on their activity and sleep data trough their devices. This might include suggestions for increasing step counts or tips for better sleep hygiene. The study team will provide a communication channel available for participants to address any technical issues or queries they might have regarding device usage. They will be instructed to wear the wearable device all the time (except when charging) and use the mattress while sleeping. Patients who do not use the device for at least 60% of the time will be excluded from the trial. Compliance of divide use will be regularly monitored by the study team.

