**Fig. 1 Fig1:**
[figure not shown]
SPIRIT diagram

The primary outcome will be the participants’ PA measurement assessed at baseline and at 6 months using the IPAQ-SF. Secondary outcomes will include changes in participants’ frailty status, biometric measurements, quality of life, and biopsychosocial assessments at baseline and at 6 months (Table 1).

**Table 1 Tab1:** Data measurements to be recorded during the study period

	Baseline	Study period	6 month follow-up
**Self-reported**	IPAQ-SF		IPAQ-SF
	IMSA		IMSA
	SF-12		SF-12
**Healthcare professional reported**	Vivifail questionnaire		Vivifail questionnaire
	BMI		BMI
	Abdominal perimeter		Abdominal perimeter
	Calf perimeter		Calf perimeter
**Sensor data**		Number of steps	
		Heart rate	
		Sleep quality	
**EHR data**	Historical clinical data	Unplanned hospital admissions	

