### Statistical analysis

A sample size of 40 participants per arm was calculated to be sufficient to detect a group difference, with the alpha set at 0.05, and the power set at 0.80. Protecting against a dropout rate of 20% over the 6-month study duration, 50 participants will be recruited and randomized into each arm (A or B). We will conduct an exploratory analysis of the recorded data. This will be based on descriptive statistics and will be used to characterize the universe of data and identify outliers and general trends. Agreement between IPAQ-SF and wearable activity will be assessed trough Cohen’s kappa. We will use McNemar’s test to compare groups at baseline and 6-month follow-up regarding the study outcomes. In addition, we will assess the impact of wearable data and PROMs in predicting unplanned hospital admissions using classification accuracy, absolute error, and ROC AUC analysis.

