## Discussion

We will employ the IPAQ-SF to measure the level of activity in all patients and therefore detect differences between patients who will be using wearables and those who will not. Despite conflicting evidence regarding the correlation with objectively measured PA, this test is highly reported in the literature and has been previously validated in Portuguese. We expect that the results of this study will contribute to better knowledge about the PA patterns of patients with MM as well as the impact of PA intervention in this population, a topic that is underexplored in the literature [16].

In addition, we aim to explore the influence of different PA patterns on other important outcomes such as PROMs and healthcare resource utilization. For this purpose, we will make use of a PROMs registry that has been developed locally for the purpose of data entry. We aim to understand the added impact of wearable data on medical information data for predicting PROMs and unplanned hospital admissions. Data from participants’ medical records will be assessed in the following fields: previous diagnosis, previous hospital episode types and specialties, previous medical procedures, biometrics (weight, height, and BMI), clinical notes, laboratory results, and drugs prescribed or administered in an inpatient setting. The recorded data will be anonymized and stored locally. We aim to understand whether there is any added impact of using this information for future modeling.

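### McNemar's test, the only test named for the study outcomes, needs paired binary data and cannot compare the two randomised arms

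*Protocol article*

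**What the plan says.** The Statistical analysis section of the protocol article gives one sentence on testing the outcomes: "We will use McNemar’s test to compare groups at baseline and 6-month follow-up regarding the study outcomes". The other statistics named there serve other purposes: descriptive summaries, Cohen's kappa for agreement between questionnaire and wearable, and accuracy, absolute error and ROC AUC for predicting unplanned admissions.

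The design is parallel and individually randomised. Under Study intervention: "Eligible participants will be randomly assigned in a 1:1 ratio to one of the following intervention arms". Both arms get activity counselling: "All Participants who are eligible and consented to participate in the study shall receive PA promotion content". The Discussion states the aim of the comparison, which is to "detect differences between patients who will be using wearables and those who will not". The sample size of 40 evaluable per arm is also described as enough to show a difference between groups.

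Under Study measures and outcomes: "The primary outcome will be the participants’ PA measurement assessed at baseline and at 6 months using the IPAQ-SF". No binary definition is given. The secondary outcomes are "changes in participants’ frailty status, biometric measurements, quality of life, and biopsychosocial assessments at baseline and at 6 months", and Table 1 lists BMI, abdominal perimeter, calf perimeter, SF-12 and IMSA among the measurements. The only activity threshold in the document is an exclusion rule, which removes "patients who are sufficiently physically active, defined with International Physical Activity Questionnaire - Short Form (IPAQ-SF) > 150 min aerobic physical activity per week".

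**The concern.** McNemar's test asks whether, among pairs of binary readings, changes in one direction outnumber changes in the other. It needs pairs, and it needs a yes/no variable. The two arms are not paired with each other, so the test has no valid form for Arm A against Arm B. Most of the outcomes it is meant to cover are numerical as collected.

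What remains is a separate before-and-after test in each arm. That answers whether people in an arm changed, not whether the wearable changed them more than counselling alone. Since both arms are counselled, some change is expected in both. Followed as written, the trial would produce no estimate, confidence interval or valid test of its randomised comparison, and readers would be left to compare two within-arm p-values.

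**Working it through.** **1. The plan's own figure.** 40 evaluable per arm with 20% dropout: 40 / (1 − 0.20) = 50 per arm, which matches the article. The 40 itself cannot be reproduced, because no effect size, SD or rates are given. Solving backwards for a two-sided alpha of 0.05 and power 0.80 (two-sidedness is my assumption), the detectable standardised difference is (1.960 + 0.842) × √(2/40) = 0.63 SD for an unadjusted comparison of two independent means. The sizing is worded as a difference between groups, so the named test is not the one that wording points to.

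**2. The test against the design (no assumptions needed).**

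| Reading of the sentence | Data needed | Data available | Result |
|---|---|---|---|
| Arm A vs Arm B | Matched pairs across arms, binary | Independent 1:1 arms | Not valid |
| Baseline vs 6 months within an arm, numerical outcome | Binary | BMI, perimeters, scores, activity amounts | Does not apply |
| Baseline vs 6 months within an arm, dichotomised outcome | Paired binary | Possible if a cut is defined | Valid, but not a test of the randomised contrast |

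**3. A conditional illustration of the third row.** Assumptions, none of them stated in the protocol as part of the outcome definition:
- IPAQ-SF is cut at 150 min/week, the exclusion threshold.
- The screening reading is also the baseline reading, so nobody starts above the cut.
- 40 are evaluable per arm.
- The true crossing rate is the same in both arms (no wearable effect) and is varied from 10% to 30%.

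With no one able to move from above to below the cut, the exact two-sided p-value for b crossers is 2 × 0.5^b:
- b = 5: 2 × 0.5^5 = 0.0625
- b = 6: 2 × 0.5^6 = 0.031

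So the test in one arm reduces to whether at least 6 of 40 (15%) crossed. Let r = P(Binomial(40, rate) ≥ 6). The chance that Arm A is significant and Arm B is not is r × (1 − r).

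| True crossing rate, both arms | Each arm significant (r) | Arm A significant, Arm B not |
|---|---|---|
| 10% | 0.21 | 0.16 |
| 15% | 0.57 | 0.25 |
| 20% | 0.84 | 0.14 |
| 25% | 0.96 | 0.04 |
| 30% | 0.99 | 0.01 |

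**4. A between-arm test on the same data.** Over the same rates, comparing the 6-month proportions of two independent arms rejects with probability 0.048 to 0.059 (pooled z) or 0.017 to 0.029 (Fisher), close to or below the nominal 0.05. For example, with 12/40 crossing in each arm, McNemar's p is 2 × 0.5^12 = 0.0005 in both arms, while Fisher's p between the arms is 1.00.

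**The case against.** The strongest defence is that a journal article condenses the plan and an unseen SAP may name a proper between-arm analysis. That would excuse silence. It does not excuse a specific test named for the wrong purpose: a SAP would either repeat the error or contradict the published protocol, and in both cases the sentence has to change.

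Other objections limit how far the point can be pushed, and they stand.
- **Eligibility and the primary outcome.** A reader might infer that the exclusion of active patients makes McNemar's test degenerate for the primary outcome, able to show only improvement. That needs two things the protocol does not say: that 150 min/week is the outcome cut, and that the screening questionnaire is the baseline reading. At another cut, or with a separate baseline reading, people could move in both directions. The same gap applies to regression to the mean as an explanation of within-arm change.
- **Size of the error.** A reader might infer a false-positive rate far above 5% throughout. The table does not support that. The misleading pattern peaks at about 0.25 near a 15% crossing rate and falls below 0.05 at 25% and 30%, where both arms usually look significant. Counting either arm alone would double these figures, but significance only in the control arm would not be taken as a benefit of the device.
- **Testing at baseline.** The sentence could be read as planning significance tests between arms at baseline. It can equally mean baseline against follow-up, so that criticism is not secure.

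**Conclusion.** The point holds, and its core rests on no assumption. The only test named for the outcomes is a paired binary test. It cannot compare two independent randomised arms, does not fit the numerical outcomes, and in its one workable form leaves the trial's main question untested. This is a wrong method as stated, and it must be corrected before analysis.

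The figures for the harm are illustrative. They depend on the assumed cut, the assumed baseline reading and the assumed crossing rates, and should be quoted as a range: with no device effect, 0.21 to 0.99 for significance within an arm, and 0.01 to 0.25 for significance in Arm A only. The stronger claim that eligibility by itself breaks the test for the primary outcome is not supported, because the protocol leaves that outcome's form undefined. If the outcome is numerical, the test does not apply at all. If it is binary at some cut, the test still does not compare the arms.

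**What to change.** Replace the McNemar sentence with a between-arm analysis:

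1. **Primary variable.** Define it in advance, for example total activity on the IPAQ-SF at 6 months.
2. **Primary analysis.** Compare the arms as randomised by ANCOVA adjusted for baseline IPAQ-SF, reporting the adjusted difference with its 95% CI. Fix the scale beforehand, or specify a rank-based version, rather than choosing after seeing the data. It must allow zero values, since inactive participants may report none and a plain log transform would fail.
3. **Secondary outcomes.** Use the same model with each outcome's own baseline for continuous measures. For binary measures at 6 months, compare the arms by logistic or risk-difference regression.
4. **Within-arm change.** Report descriptively only.
5. **Sample size.** State the effect that 40 per arm detects under the chosen test. For an unadjusted two-sided comparison of means it is about 0.63 SD, back-solved here because the protocol gives none.

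The cost is a few lines in the protocol and SAP. No extra data, visits or participants are needed to make the change.

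### The only stated outcome test, McNemar's, gives no between-arm estimate and takes no covariate, although baseline values are collected in everyone; a baseline-adjusted between-arm model should replace it.

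*Protocol article*

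**What the plan says.** Under Study measures and outcomes, all participants attend a baseline visit and a 6-month visit. On the primary outcome: "The primary outcome will be the participants’ PA measurement assessed at baseline and at 6 months using the IPAQ-SF". On the others: "Secondary outcomes will include changes in participants’ frailty status, biometric measurements, quality of life, and biopsychosocial assessments at baseline and at 6 months". Table 1 lists IPAQ-SF, IMSA, SF-12, Vivifrail, BMI and the abdominal and calf perimeters at both visits.

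Under Statistical analysis, the one test named for these outcomes is McNemar's, to be used "to compare groups at baseline and 6-month follow-up regarding the study outcomes". No model, covariate or baseline adjustment is mentioned. For a significance level of 0.05 and 80% power, the size is given as follows: "A sample size of 40 participants per arm was calculated to be sufficient to detect a group difference".

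The intended contrast is between the randomised arms. The Discussion says that IPAQ-SF is used to find differences between patients with and without wearables. Under Inclusion and exclusion criteria, patients reporting more than 150 minutes of aerobic activity per week on IPAQ-SF are excluded.

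**The concern.** McNemar's test compares two linked binary measurements through the discordant pairs. Two readings of the sentence are possible, and neither gives the comparison that the trial needs.

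- **Visit against visit within participants.** The pairing is valid, but the test addresses change over time, within one arm or over both arms pooled. Both arms receive activity counselling, so change in both is to be expected.
- **Arm against arm at each visit.** The arms are independent groups and no matching is described, so there are no pairs to analyse. A comparison at baseline would also be uninformative, because under randomisation any difference there is due to chance.

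The test also needs a dichotomy, and none is fixed for IPAQ-SF, SF-12, IMSA, BMI or the perimeters.

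At stake is, first, whether the trial produces an arm effect with a confidence interval at all. Second, if the test is merely exchanged for an unadjusted two-sample comparison, baseline information already collected stays unused with about 40 evaluable participants per arm.

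**Working it through.** **1. The article's own figures.** Inputs from Statistical analysis: 40 evaluable per arm, alpha 0.05, power 0.80, dropout 20%, 50 randomised per arm.

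- Dropout step: 40 / (1 − 0.20) = 50. This reproduces.
- The 40 cannot be reproduced, because no effect size, SD, event rate or sidedness is given. Assuming a two-sided test of two means, it implies d = (1.960 + 0.842) × √(2/40) = 0.626 (0.634 with the t distribution). For two proportions it would correspond to, for example, 20% against 49%.

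**2. What McNemar's test responds to.** Suppose IPAQ-SF is cut at the 150-minute entry limit. Everyone is then inactive at baseline, and the active-to-inactive cell is empty by design. Simulating the exact test with 20% becoming active in both arms, hence no arm effect, it rejects in 83% of single arms of 40 and in over 99% of trials when the arms are pooled. A significant result would therefore say nothing about the wearable.

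**3. What baseline adjustment adds to a between-arm analysis.** Assumptions: continuous outcome, two-sided alpha 0.05, 40 per arm, d = 0.626. Adjustment multiplies the residual variance by (1 − ρ²), where ρ is the baseline to 6-month correlation within arms. Power = Φ(2.802 / √(1 − ρ²) − 1.960). The article gives no ρ, so a range is shown.

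| ρ | Variance factor | Power | Gain (points) | n per arm for 80% |
|---|---|---|---|---|
| 0.1 | 0.99 | 80.4% | 0.4 | 40 |
| 0.3 | 0.91 | 83.6% | 3.6 | 37 |
| 0.4 | 0.84 | 86.4% | 6.4 | 34 |
| 0.5 | 0.75 | 89.9% | 9.9 | 30 |

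**4. Effect of the entry limit on ρ.** In a simulated bivariate normal truncated above on baseline, with 30% to 70% of the source population under the limit, an unrestricted ρ of 0.5 falls to about 0.28 to 0.38. From the formula in step 3, that range gives about 83% to 86% power, a gain of about 3 to 6 points.

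**5. Change score under the same truncation.** Take unrestricted ρ = 0.6 and unit SDs, with baseline cut at the median. The baseline variance becomes 1 − 2/π = 0.363.

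- 6-month value: 0.36 × 0.363 + 0.64 = 0.77
- Change: (0.6 − 1)² × 0.363 + 0.64 = 0.70
- Baseline-adjusted: 0.64

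In this example the change score is less variable than the 6-month value alone, and the adjusted analysis is best.

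**The case against.** The strongest objection is that a journal article leaves covariates to the analysis plan, so a missing covariate list is no finding. That is right for a bare omission. It does not cover this case, because the article names the test for the study outcomes and that test can supply neither an arm effect nor an adjusted one.

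It can also be said that the power figures belong to a design the article does not state: a continuous outcome and a two-sample comparison. This stands. McNemar's test and Cohen's kappa both suggest categories. If IPAQ-SF were cut at 150 minutes, the binary baseline would be the same for everyone and adjusting for it would add nothing. A continuous baseline in minutes could still help, by an unknown amount.

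Three stronger readings are tempting and are not supported:

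- **That an unadjusted between-arm effect is planned and needs only a covariate.** The stated test yields no between-arm effect to adjust.
- **That about 10 points of power are being lost.** This needs ρ = 0.5 in the enrolled sample, which is optimistic for the primary outcome given the entry limit.
- **That the entry limit makes a change score noisier than the 6-month value.** The usual threshold of ρ = 0.5 assumes equal SDs, but truncation also shrinks the baseline SD, and step 5 gives a counterexample.

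**Conclusion.** The point holds in this form: the named test does not answer the between-arm question and cannot use the baseline values as covariates, although these are recorded in all participants. The mismatch between test and aim follows from the text and needs no assumption.

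The added precision from baseline adjustment is real in principle, but its size is assumed: 0.4 to about 10 points of power for ρ from 0.1 to 0.5, with the lower part more likely for IPAQ-SF. It may be larger for BMI and the perimeters, which have no comparable entry limit and may correlate more strongly over 6 months; the article gives no figures on this. The adjustment itself is a matter of efficiency. The lack of a between-arm estimate is the more serious part.

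**What to change.** Replace McNemar's test with one between-arm estimate of 6-month IPAQ-SF activity from a linear model with arm and the continuous baseline IPAQ-SF value, both measurements on the same scale. Use a transformation or robust standard errors if the data are skewed. Report the adjusted difference with its 95% CI.

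Use the same model for the continuous secondary outcomes (SF-12, IMSA, BMI and the perimeters), each with its own baseline value. If an outcome is kept as categories, use logistic or ordinal regression with arm and the baseline value, continuous where available. Drop any between-arm test at baseline.

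The cost is analysis wording and one degree of freedom per model. No new data, visits or participants are needed.
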